### Interventions

#### Control group.

Participants assigned to the control group will receive the standard treatment for RCRSP. This will involve standardized therapeutic exercises, performed for 25 minutes, three times per week, over a 12-week period. The intensity of the exercises will be tailored to each participant, using the Rating of Perceived Exertion (RPE) scale, aiming for intensities between 5 and 8 on a 0–10 scale. The exercises and progressions used will be the ones described in the PASE trial [40], yet the program will be adapted to divide the exercises into 3 days. Therefore, 3 exercises will be carried out during the first session of the week, 3 exercises during the second session and 4 exercises during the final session (S3 File).

#### Experimental group.

Participants in the experimental group will follow a treatment program that combines the standard treatment with an IVR intervention program. For the first 4 weeks, participants will undergo IVR treatment, and in the following 8 weeks, they will follow the same treatment as the control group.

Participants will complete up to 12 sessions of IVR, using a head-mounted display (HMD) of Meta Quest III and a hand tracking system (Meta VR, Facebook, California) to interact with the therapeutic software “Dynamics PainRehab” (Dynamics VR Rehab, Seville, Spain). The Meta Quest III HMD was selected due to its commercial availability, widespread use, minimal visual latency, and ease of use for participants. The “Shoulder PainRehab” app will be used, which features multisensory inputs (visual and auditory), high-quality graphics, and head and hand tracking, allowing for an immersive experience. Additionally, the IVR program will incorporate embodiment strategies via full-body virtual avatars, which have been associated with greater hypoalgesic and sensorimotor effects during IVR interventions (Fig 2).

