**Materials and methods:**

A single-blind, multicentre randomized clinical trial will be conducted. Participants will be randomly assigned to two groups: the control group will undergo a three-month exercise program, while the intervention group will receive an IVR program for the first month, followed by the same exercise program for the control group during second and third months. Clinical, clinimetric, and biomarker variables will be assessed at baseline and at follow-ups at 1, 2, and 3 months.

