**Conclusions:**

This study protocol outlines a novel approach to managing chronic rotator cuff-related shoulder pain by integrating IVR with exercise-based physiotherapy. The results will provide valuable insights into the additive effects of IVR on variables such as pain, function, psychosocial factors and biological markers, potentially informing future rehabilitation strategies and enhancing patient outcomes in musculoskeletal care.

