**Fig 2 pone.0341215.g002:**
[figure not shown]
Immersive virtual reality multisensory environment with integrated full-body virtual avatar. Dynamics PainRehab® (Dynamics VR Rehab, Seville, Spain). All images have been reproduced with the permission of the respective company, and all rights to these images are owned by the respective rights holders.

Participants will receive an IVR session three times a week for 20 minutes within the virtual environment, completing the necessary 12 training sessions. They will be supervised by an experienced physiotherapist. Prior to the start of the IVR program, all participants will play a familiarization game with the IVR system during 2 sessions, regardless of their clinical assessment findings, to become accustomed to using the VR system.

The behavioral IVR program consists of three weekly sessions, progressing through six levels of difficulty. The program begins with 50% of the shoulder’s range of motion (ROM), with difficulty increasing by 10% increments in maximum ROM, reaching 100% by the final stages. The interventions will be delivered individually to each participant. If the participant experiences adverse effects such as severe cybersickness, dizziness, musculoskeletal injury, or persistent increase in pain exceeding 7/10 for more than two consecutive sessions the intervention will be discontinued.

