## Results

According to the recommendations of the Initiative on Methods, Measurement, and Pain Assessment in Clinical Trials (IMMPACT), this study will incorporate multiple measures to evaluate changes in pain intensity, health-related quality of life and functioning, as well as global ratings of improvement [41]. Similarly, the assessment of domains will follow expert consensus from the OMERACT Shoulder Working Group, aligned with the Core Domain Set for Shoulder Disorders [42].

Clinical and clinimetric outcomes will be assessed at baseline and at follow-ups at 1-, 2- and 3-months following treatment initiation. Biomarkers will be measured at baseline and at 1- and 3-months follow-ups (Figs 1 and 3).

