### Allocation and randomization

Individuals meeting the inclusion criteria will be randomly allocated to one of two treatment arms: (1) IVR plus exercise or (2) exercise alone.

Each patient will be assigned an alphanumeric code for identification, thus respecting their anonymity. To carry out the simple randomization procedure, the principal investigator will receive a list of the alphanumeric codes of the participants and will carry out a random assignment of the subjects in the 2 intervention groups using the SPSS statistical program. Allocation concealment will be ensured using opaque, sealed envelopes. A designated research assistant, independent of the assessment team, will open each envelope to assign participants to their respective intervention or control groups.

Participants will be randomized into intervention and control groups using a predefined randomization scheme, following the provision of informed consent and confirmation of clinical eligibility.

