Whereas most IVR research has been focused on acute pain or short time interventions, this study is focused on a prevalent form of chronic pain with a longer time horizon to test for evidence of additional benefits within a first line treatment recommendation. Given the current paucity of rigorous randomized controlled trials evaluating the efficacy of IVR compared to standard care or a wait-and-see approach, there is a pressing need for high-quality evidence to inform clinical decision-making. Encouraging such studies is essential to guide stakeholders in the effective implementation of IVR-based interventions in daily clinical practice. Likewise, establishing adequate dosimetry and reporting user experience factors has been recommended to guide IRV-based exercises in evidence-based clinical practice. The present study follows international recommendations for reporting RCTs, including those of CONSORT and TIDieR, which guarantees the reproducibility of the study, and the interventions performed.

Although the study design and methods have been meticulously considered, several limitations and practical considerations need to be addressed. One potential limitation of the study is the possibility of adverse events such as “cybersickness”, particularly in older adults or those unfamiliar with digital technology. To address this, we have designed a training session with gradual introduction to familiarize participants with the IVR system and will provide ongoing technical support throughout the study. Moreover, participants will be actively monitored for any health-related issues or adverse event throughout the course of the trial.

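### The protocol claims an additive effect of IVR, but IVR takes the place of 4 of the 12 exercise weeks, so the contrast is one of substitution

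*Protocol article*

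**What the plan says.** **Schedule.** The Control group section defines standard treatment as exercise "performed for 25 minutes, three times per week, over a 12-week period". The Experimental group section opens by saying that the arm combines standard treatment with IVR. It then gives the order, with 4 weeks of IVR before any exercise: "participants will undergo IVR treatment, and in the following 8 weeks, they will follow the same treatment as the control group". The Abstract (Materials and methods) agrees that this arm "will receive an IVR program for the first month, followed by the same exercise program for the control group during second and third months". The IVR dose follows Fig 2: "Participants will receive an IVR session three times a week for 20 minutes within the virtual environment, completing the necessary 12 training sessions". The Results section sets the visits: "Clinical and clinimetric outcomes will be assessed at baseline and at follow-ups at 1-, 2- and 3-months following treatment initiation".

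**Claims.** The aim at the end of the Introduction is to compare IVR combined with standard care against standard care alone. Allocation and randomization labels the arms "1) IVR plus exercise or (2) exercise alone", and the biomarker analysis repeats that pairing. The Abstract's Conclusions state: "The results will provide valuable insights into the additive effects of IVR on variables such as pain, function". The Discussion presents the trial as having a "longer time horizon to test for evidence of additional benefits within a first line treatment recommendation".

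**The concern.** An additive effect is what a treatment contributes when both arms receive the same background care. Here the background care differs. The experimental arm has had less standard exercise than the control arm at every follow-up visit, and none at month 1.

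What is at stake is how the result may be worded. A favourable month-3 difference would support the replacement sequence, not IVR on top of a full exercise course. A small or absent difference would be compatible with IVR having done as well as the exercise it displaced. The closing Conclusions section says favourable results should lead to the programme being considered for clinical practice and health policy. A reader acting on that needs to know whether the evidence concerns adding IVR or substituting it.

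**Working it through.** **Inputs.** Exercise is 3 sessions a week of 25 minutes, for 12 weeks in the control arm (Control group) and for 8 weeks, after the first 4, in the experimental arm (Experimental group). IVR is 3 sessions a week of 20 minutes for 4 weeks. Visits are at 1, 2 and 3 months, taken as weeks 4, 8 and 12, since the protocol treats the first month and the first 4 weeks as the same period.

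**The plan's own figure.** IVR sessions: 3 × 4 = 12, which matches the 12 stated.

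**Formulas.** Let w be weeks since the start.
- Control exercise sessions = 3w.
- Experimental exercise sessions = 3(w − 4), for w of at least 4.
- Exercise minutes = 25 × exercise sessions.
- IVR minutes = 20 × 12 = 240 from month 1 onward.

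| Visit | Control: exercise | Experimental: exercise | Experimental: IVR | Exercise ratio |
|---|---|---|---|---|
| Month 1 (w = 4) | 12 sessions, 300 min | 0 sessions, 0 min | 12 sessions, 240 min | 0% |
| Month 2 (w = 8) | 24 sessions, 600 min | 12 sessions, 300 min | 12 sessions, 240 min | 12/24 = 50% |
| Month 3 (w = 12) | 36 sessions, 900 min | 24 sessions, 600 min | 12 sessions, 240 min | 24/36 = 67% |

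The exercise deficit is 12 sessions (300 minutes) at every visit. At month 3 this is 12/36, one third of the standard programme. Total scheduled contact is 12 + 24 = 36 sessions against 36, and 240 + 600 = 840 minutes against 900. The two IVR familiarization sessions are not counted, as their length is not given.

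**What month 3 estimates.** Write Y(IVR, 24) for the outcome after IVR then 24 exercise sessions, Y(0, 24) after the same 24 sessions without IVR, and Y(0, 36) after the full course. In expectation:

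Y(IVR, 24) − Y(0, 36) = [Y(IVR, 24) − Y(0, 24)] + [Y(0, 24) − Y(0, 36)]

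The first bracket is the effect of IVR placed before a shortened exercise course. The second is the effect of losing 12 exercise sessions. No arm receives the middle condition, so the brackets cannot be separated. The add-on effect, Y(IVR, 36) − Y(0, 36), would need an arm with IVR and all 36 exercise sessions, which is also absent. The mixed model in the Statistics section estimates group differences at the visits and cannot supply either missing condition.

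The sample size does not enter this argument.

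**The case against.** The best defence is that nothing is hidden. The Abstract gives the full sequence, and the arm does receive both IVR and exercise over 12 weeks, so *combined* can fairly mean a sequential package. On that reading, months 2 and 3 compare the package with exercise throughout. This stands. A reader might infer that the trial cannot answer its stated question at all, but the documents do not support that: the comparison of two 12-week strategies is randomised and sound.

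The design also has a merit. Scheduled sessions are equal at 36 and 36. IVR on top of full exercise would have mixed IVR with extra supervised contact, in a trial with unblinded participants and a self-reported primary outcome. Substitution is a legitimate choice, and this point does not criticise it.

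Some of the wording is also open to a softer reading. The arm label is literally true over 12 weeks, and the Discussion phrase could mean IVR embedded in first-line care. That is fair. It leaves the Abstract's additive claim as the plain mismatch, and the objective, labels and Discussion as text that invites the same reading. Describing the sequence openly does not make the contrast additive.

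**Conclusion.** The point holds as a mismatch between schedule and claim. The experimental arm has had 12 fewer standard exercise sessions than the control arm at every visit (0 against 12, 12 against 24, 24 against 36), and no visit isolates IVR added to equal standard care. This rests on the schedule as written and on sessions being delivered as planned; it needs no assumption about effect sizes.

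Three stronger readings are tempting but not supported:

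- **That the first third of the exercise programme is lost.** The text fixes calendar weeks. It does not say whether the experimental arm then starts the progressive programme from its beginning or joins it part-way. Only 4 of the 12 weeks can be claimed.
- **That the month-3 effect equals the IVR effect minus the effect of 4 weeks of exercise.** The contrast at month 1 is simply IVR against exercise. By month 3, order, carry-over and interaction with later exercise may all contribute, so the formula needs an additivity assumption that the protocol does not make.
- **That the protocol intends to read a null result as no benefit of IVR, or wrongly omits a statement on equivalence.** No section says the former. The latter is ordinary content for an analysis plan, which is not shown.

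**What to change.** Reconcile the objective, arm labels and planned conclusions with the schedule, leaving treatment unchanged:

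1. State the contrast as *a 12-week programme in which IVR takes the place of 4 of the 12 weeks of exercise, versus 12 weeks of exercise*, and align the arm labels with it, including in the biomarker analysis.
2. Report month 1 as IVR versus exercise, and month 3 as the full sequence versus exercise throughout.
3. Remove additive effects (Abstract) and additional benefits (Discussion) as claims that the trial will support.

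This takes the schedule as written. If the investigators intended something different, the intervention sections must be reconciled with the aim, and that decision is theirs. The cost is a revision of wording before the results are analysed, and a more modest claim. Patient numbers and the analysis model do not change.

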**Fig 2 pone.0341215.g002:**
[figure not shown]
Immersive virtual reality multisensory environment with integrated full-body virtual avatar. Dynamics PainRehab® (Dynamics VR Rehab, Seville, Spain). All images have been reproduced with the permission of the respective company, and all rights to these images are owned by the respective rights holders.

Participants will receive an IVR session three times a week for 20 minutes within the virtual environment, completing the necessary 12 training sessions. They will be supervised by an experienced physiotherapist. Prior to the start of the IVR program, all participants will play a familiarization game with the IVR system during 2 sessions, regardless of their clinical assessment findings, to become accustomed to using the VR system.

The behavioral IVR program consists of three weekly sessions, progressing through six levels of difficulty. The program begins with 50% of the shoulder’s range of motion (ROM), with difficulty increasing by 10% increments in maximum ROM, reaching 100% by the final stages. The interventions will be delivered individually to each participant. If the participant experiences adverse effects such as severe cybersickness, dizziness, musculoskeletal injury, or persistent increase in pain exceeding 7/10 for more than two consecutive sessions the intervention will be discontinued.

#### Intervention adherence.

Adherence to intervention in both groups will be measured by quantifying the number of sessions completed by each subject.

## Results

According to the recommendations of the Initiative on Methods, Measurement, and Pain Assessment in Clinical Trials (IMMPACT), this study will incorporate multiple measures to evaluate changes in pain intensity, health-related quality of life and functioning, as well as global ratings of improvement [41]. Similarly, the assessment of domains will follow expert consensus from the OMERACT Shoulder Working Group, aligned with the Core Domain Set for Shoulder Disorders [42].

Clinical and clinimetric outcomes will be assessed at baseline and at follow-ups at 1-, 2- and 3-months following treatment initiation. Biomarkers will be measured at baseline and at 1- and 3-months follow-ups (Figs 1 and 3).

**Fig 3 pone.0341215.g003:**
[figure not shown]
Study timeline.

To ensure consistency and minimize measurement bias across sites, all outcome assessors have undergone standardized inter-rater reliability training. Specifically, the principal investigator personally conducted on-site training sessions in both Spain and Chile prior to the start of data collection. In this respect, assessors were trained using identical materials and procedures, including operational definitions, scoring guidelines, and case simulations.

### Primary outcome

Pain intensity: it will be assessed using the 11-point Numeric Pain Rating Scale (NPRS), ranging from 0 (no pain) to 10 (worst imaginable pain). The NPRS has demonstrated good to excellent test-retest reliability (Intraclass Correlation Coefficient [ICC] = 0.63–0.92) [43,44]. Pain intensity will be evaluated during the most painful reported movement. Therefore, primary outcome is pain intensity change from baseline.

### Secondary outcomes

#### Clinical variables.

Shoulder external rotation isometric strength: it will be measured using the MicroFET 2 MT Digital Handheld Dynamometer (Hoggan Health Industries, West Draper, UT). Handheld dynamometry has shown good to excellent intra-rater reliability for shoulder isometric strength assessment (ICC = 0.87–0.99) [45,46].

Hand grip strength: it will be assessed by using the Jamar hand dynamometer (Sammons Preston Rolyan, Bolingbrook, IL), which has demonstrated good to excellent intra-rater reliability for isometric grip strength (ICC = 0.85–0.98) [47].

Active shoulder range of motion: it will be assessed using a smartphone inclinometer application (Plaincode Software Solutions, Gunzenhausen, Germany) in flexion, abduction, external rotation at 0º and 90º of abduction, and internal rotation at 90º of abduction. This method has demonstrated excellent inter-rater reliability and validity in symptomatic populations (ICC > 0.80) [48].

#### Biomarkers.

Venous blood samples will be drawn from the antecubital vein, centrifuged, aliquoted, and stored at –80°C until analysis. These procedures will be carried out at the Exercise Physiology Research Laboratory of the UFV by external laboratory nurses from Eurofins Megalab, who will be responsible for both sample collection and biomarker analysis. The biomarkers to be analyzed include:

C-reactive protein (CRP), an oxidative stress and inflammation marker.Calcitonin Gene-Related Peptide (CGRP), a neuropeptide involved in the modulation of nociceptive signalling and that has been shown to represent a neurobiological marker of chronic pain and inflammation [37].

Biomarkers measurements will only be made on the Spanish arm of the study, and not in the Chilean arm. This decision was driven by logistical and budgetary constraints. In this respect, biomarker-related analyses will be explicitly stratified, and results will be presented separately for the Spanish sample.

#### Clinimetrics.

Shoulder disability: it will be assessed using the Spanish version of the Shoulder Pain and Disability Index (SPADI), a 13-item self-report questionnaire originally developed to evaluate shoulder pain and disability [49]. The SPADI has demonstrated adequate discriminative capacity across varying clinical conditions (Roy et al., 2009). The cross-culturally adapted Spanish version retains 13 items assessing pain and functional impairment and has been validated for use in both clinical and research settings [50].

Quality of life: it will be measured using the SF-12 (Short Form Health Survey), which evaluates eight dimensions of health-related quality of life. The SF-12 has demonstrated good reliability and validity across various populations [51].

Fear of movement: it will be evaluated using the Tampa Scale for Kinesiophobia (TSK), which has demonstrated high reliability and internal consistency (ICC = 0.76–0.90) [52].

Pain-related avoidance behaviours: daily activity avoidance will be assessed using the Photographic Series of Daily Activities for Shoulder Pain Patients (ADAP-Shoulder Scale) [53]. The scale includes 15 photographs categorized into three domains: free movement (5 items), high effort (7 items), and self-care (3 items), with total and domain scores ranging from 0 (no avoidance) to 100 (extreme avoidance). The scale has demonstrated high internal consistency (α = 0.89–0.92) and excellent test-retest reliability (ICC = 0.94) [54,55].

Pain hypervigilance: it will be assessed using the Pain Vigilance and Awareness Questionnaire (PVAQ), a validated instrument with high internal reliability designed to measure attention to pain [56].

Pain self-efficacy: it will be measured with the Pain Self-Efficacy Questionnaire (PSEQ), which assesses a patient’s confidence in performing activities despite pain. The PSEQ has shown excellent reliability and validity in chronic pain populations [57].

Pain-related motor and functional deficits: it will be assessed using the 16-item version of the Biopsychosocial Pain and Movement Questionnaire (CBioD-MOV), which covers four subscales: physical activity self-efficacy, disability, movement avoidance behaviour, and perceived functional capacity. The questionnaire uses a 5-point Likert scale with a total score range of 0–62. The Spanish version has demonstrated good to excellent measurement reliability [58].

Implicit motor imagery performance: it will be evaluated through a left/right shoulder judgment task, in which participants are shown shoulder images in various postures and must identify whether the shoulder is left or right as quickly and accurately as possible. The task will be conducted using the Recognise™ software (noigroup.com, Adelaide, Australia), involving 30 randomized images. The task has shown adequate reliability [59].

Sleep quality: The participants’ sleep quality will be assessed using the Pittsburgh Sleep Quality Index (PSQI), a self-reported questionnaire designed to evaluate various aspects of sleep [60,61]. It comprises 19 items, which are organized into seven components: subjective sleep quality, sleep latency, sleep duration, habitual sleep efficiency, sleep disturbances, use of sleep medication, and daytime dysfunction. The total PSQI score is calculated by summing the scores of these seven components.

Treatment adherence will be measured by quantifying the number of sessions attended by each participant. Satisfaction and enjoyment regarding received interventions will also be measured by using a 0–10 Numeric Rating Scale at 1 month- and 3 months- follow ups.

